### Study population

#### Inclusion criteria

Participants will be eligible for the study given the following criteria upon enrolment for the study:
Age 6–29 yearsRegistered member of MLSE LaunchPadAttending programming at MLSE LaunchPadAbility to speak, understand and read EnglishPhysically able to participate in programming with or without the use of assistive devices-Recruited within 8 weeks of commencing program participation.

MLSE LaunchPad defines ‘youth facing barriers’ as ‘youth who may need greater supports and services to reach their full potential’, including low income, racialized, Indigenous, new to Canada, LGBTQ2S, and homeless or underhoused youth; youth in care or leaving care; and youth in conflict with the law. Demographic data will be collected in self-report surveys and through member registration and used to define characteristics of the population. No formal process is used to ensure youth accessing MLSE LaunchPad’s programs meet the stated criteria for ‘youth facing barriers’, and no youth are excluded from programming based on these criteria; however, the neighborhood demographics and outreach strategy have to date resulted in program participation by youth who meet the criteria outlined.

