#### Recruitment

Recruitment of participants began in February 2017 and will continue through September 2019. Participants will be followed for up to two years with data collection to conclude by March 31, 2020. During program registration and within the first week of each program cycle, new participants (and parents/guardians if applicable) will be given information about the research study and the requirements of research participation. If the participant indicates interest, they (and the parent/guardian where applicable) will be taken through the consent process.

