#### Intervention

Programs (described in Table 2) include a mix of sport plus programs, developed by an in-house team of sport programmers, and plus sport programs, several of which have been developed collaboratively with community partner organizations with similar target demographics and intended PYD impacts. The collaborative programming model engages the expertise of the aforementioned community partner organizations; academic partners with knowledge of PYD and SFD; and partners in the broader sport and physical education sectors. Each program falls under one of the following program pillars: Healthy Mind, Healthy Body, Ready for School, or Ready for Work. All programs incorporate sport and physical activity as a part of a psychologically and physically safe learning environment. An evidence-based coaching philosophy creates consistent coaching standards across programs, ensuring that life skills teaching is explicitly incorporated into all programs and that peer-peer and peer-leader relationships are emphasized. Coaches delivering programs are trained in life skills development and transference and physical literacy and fundamental movement skills by academic partners to provide high-quality, evidence-based and intentionally designed youth SFD programming based on the program theory explicated in the MLSE LaunchPad Theory of Change (see Fig. 1). Youth mentors, who are present in the facility before, during and after program times, act as resources to participants and facilitate connections with peers, leaders, and community resources. Youth mentors play a key role in the teaching of life skills by modelling positive behaviours and using teachable moments and are considered a key element of programming for all 3 age groups.

**Table 2 Tab2:** Program Descriptions

Age	Available Programming	Expected Outcomes	Evaluation Tool

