Programs for the 6–12 and 13–18 year-old cohorts will be delivered in 8-week cycles with 5 cycles each year. As research participants may participate in multiple recreational programs concurrently, volume (total program hours) and duration (number of program weeks) of participation will be used as mediating variables in analyses to examine the dose-response on objectives outlined in Table 1. All programs will include life skills development using coaching strategies discussed by Camiré et al. (2011) [19], focused on 7 life skills identified in the MLSE LaunchPad Theory of Change: grit, resilience, self-esteem, self-regulation, critical thinking, social competence, and leadership.

Participants aged 19–29 years will be offered plus sport programming developed in collaboration with local community organizations offering occupational skills training and other employment services. These agencies will demonstrate strong histories of positive youth impact and will work with MLSE LaunchPad’s sport programmers to deliver integrated employment training and sport/physical activity programming. The addition of sport and physical activity is expected to offer a different context for reiteration of in-class themes (i.e. leadership and other key life skills) and to encourage increased long-term physical activity participation. The priority of this age group will be the Ready for Work pillar. Secondary emphasis will be on the Healthy Body and Healthy Mind pillars. Due to the training nature of these programs, the format will differ from the programs offered for youth aged 6–18, and programs will generally be delivered for 4 or more hours per day, 5 days per week for 8–10 weeks, with sport programming delivered in 1-h sessions 2 days/week.

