#### Outcomes

Participants will complete a baseline assessment within 2 weeks of recruitment. Follow-up research assessments will take place at 6 months, 12 months, and 24 months from the baseline assessment with data collection concluding March 31, 2020. Outcomes have been identified based on the program theory illustrated in the MLSE LaunchPad Theory of Change (See Fig. 1). Outcomes and indicators for the primary objectives are detailed in Table 3.

**Table 3 Tab3:** Outcomes for Primary Objectives

Participants aged 6–12	
a) Increased physical literacy	Indicator:
	PLAYself Physical Literacy Assessment for Youth [36] 22-item graded self-report scale used to evaluate level of physical literacy
b) Physical activity minutes/day	Indicator:
	One-week pedometry producing at least 3 days of valid data with a minimum wear time of 10 h/day
c) Continued engagement in sport	Indicator:
	Self-report of regular sport/physical activity participation
Participants aged 12–18	
a) Life skills:	Indicator:
i. Critical Thinking ii. Resilience iii. Self-esteem iv. Self-regulation v. Social Competence vi. Grit	Critical Thinking in Everyday Life Scale [37] 20-item self-report Likert scale used to measure use of critical thinking skills including reasoning, enquiry, analysis/information processing, flexibility, and evaluation Child & Youth Resilience Measure [38] 12-item self-report scale used to measure ability to sustain well-being Rosenberg Self Esteem Scale [39] 10-item self-report Likert scale used to assess global self-esteem Motivation and Self-Regulation Subscale; derived from the School Attitudes Assessment Survey [40] 4-item self-report Likert scale used to measure ability to initiate and continue behaviours required to achieve academic goals Social Competence Scale for Teenagers [41] 9-item self-report scale used to measure positive social skills necessary to get along well with others and function constructively in groups Grit Scale [42] 8-item self-report scale used to measure stamina in dimensions of effort and interest
b) Academic Performance:	Indicator:
i. School Attendance ii. Academic Performance iii Academic Attainment	Self-report of number of missed school days over past two weeks measured as a percentage GPA as per last report card; failed courses marked as “R” on TDSB report cards will be input as 45% Self-report of highest grade/level completed
c) Physical Outcomes	Indicator:

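### Baseline may fall up to 10 weeks after programming starts, so a pre-program value is not guaranteed and some outcomes can already be met at baseline

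*Protocol article*

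**What the plan says.** All references are to the protocol article.

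- **Entry.** Under Inclusion criteria, participants must already be attending programming and must be "Recruited within 8 weeks of commencing program participation".
- **Baseline.** Under Outcomes, "Participants will complete a baseline assessment within 2 weeks of recruitment". The visits at 6, 12 and 24 months are counted from baseline. The Abstract instead describes them as times of program participation.
- **Approach to families.** Recruitment states: "During program registration and within the first week of each program cycle, new participants" receive study information, and those interested go on to consent.
- **Program length.** Under Core programming, programs for ages 6–12 and 13–18 "will be delivered in 8-week cycles with 5 cycles each year". Training for ages 19–29 generally runs "5 days per week for 8–10 weeks".
- **Content.** Under Intervention, "All programs incorporate sport and physical activity as a part of a psychologically and physically safe learning environment".
- **Outcomes.** In Table 3, self-reported regular sport or physical activity is an outcome in all three cohorts. For ages 19–29, a place in training counts alongside a job or an apprenticeship.
- **Design and analysis.** Study design describes one arm with within-subject comparison. Data analysis tests the main effect of time.

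**The concern.** With no control group, the estimated effect is the change from baseline, so baseline has to represent the state before exposure. The rules do not secure that. A participant can finish a whole cycle or training program, be recruited, and only then give the value labelled baseline. Any gain made by then drops out of the estimate.

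Two outcomes have a further difficulty. Every participant is attending programs that include sport, and many aged 19–29 may be in a partner training program. If those activities count as regular sport or as a training place, the outcome can be positive at baseline through enrolment itself. There is then little room for the hypothesised increase, and a trainee may even appear to decline once the course ends.

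The dose analysis is also exposed. For ages 6–12, Data analysis measures dose by programs attended during study participation. A program completed before baseline may then not count as dose, although its effect is already in the baseline score.

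**Working it through.** **1. Maximum lag from program start to baseline**

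Inputs: recruitment up to 8 weeks after starting (Inclusion criteria); baseline up to 2 weeks after recruitment (Outcomes).

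- Outer limit: 8 + 2 = 10 weeks.
- Against an 8-week cycle: 10/8 = 1.25 cycles.
- Against training of 8–10 weeks: 10/10 = 1.00 to 10/8 = 1.25 programs.
- If recruitment happens in the first week, as the Recruitment section describes: 1 + 2 = 3 weeks at most.

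**2. The plan's own power figure**

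Only the physical literacy calculation for ages 6–12 is given with its inputs (Sample size): means 1201 and 1277, SD 258.8, n = 150, stated power 94.9%.

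- d = (1277 − 1201)/258.8 = 76/258.8 = 0.294.
- One-sample normal approximation, two-sided alpha 0.05 (assumed; not stated): power = Φ(d√n − 1.96) = Φ(0.294 × √150 − 1.96) = Φ(3.597 − 1.960) = 94.9%. The stated figure is reproduced.

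**3. Share of the change that precedes baseline**

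Assumption: gains accrue at a constant rate from program start and continue through follow-up. Visits are timed from baseline, so a lag of L weeks puts a visit planned at w weeks at week w + L of programming. The share before baseline is L/(w + L).

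For power, the planned difference of 76 points is read as the total change from program start to the visit, so the observable part is d × w/(w + L).

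| Lag | Visit | Share before baseline | Power, n = 150 |
|---|---|---|---|
| 0 weeks | any | 0% | 94.9% |
| 3 weeks | 6 months | 3/29 = 10% | 89.7% |
| 3 weeks | 12 months | 3/55 = 5% | 92.5% |
| 3 weeks | 24 months | 3/107 = 3% | 93.8% |
| 10 weeks | 6 months | 10/36 = 28% | 73.8% |
| 10 weeks | 12 months | 10/62 = 16% | 85.5% |
| 10 weeks | 24 months | 10/114 = 9% | 90.7% |

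Worked line, 10 weeks at 6 months: Φ(3.597 × 26/36 − 1.960) = Φ(0.638) = 73.8%. Each line applies one lag to every participant.

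If gains came early and half of the change preceded baseline, power would be Φ(3.597 × 0.5 − 1.960) = 44%.

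**4. Sport and training outcomes**

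No arithmetic is possible. Entry requires attendance, all programs include sport, and the sport item asks about regular participation. The training item counts a place in training, and the training programs for ages 19–29 are partner programs. Nothing in the article includes or excludes facility or partner programs when these items are scored.

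**The case against.** The strongest reply is that 10 weeks is an outer limit, not the usual case. Families are approached at registration and "within the first week of each program cycle", so many baselines may fall before the first session or within about three weeks of it. This stands. A reader might infer that the study has no pre-program values at all, but the documents support only that none is guaranteed. The early approach sets no limit; the 8-week rule does.

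A reader might also see a contradiction between the early approach and the 8-week limit. There is none: one describes when families are approached, the other how late a new participant may enter.

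It is tempting to say that the sport and training outcomes are already met at baseline. That goes too far. The item wording is not shown, regular is not defined, one hour a week of Learn to Play need not qualify, and participants aged 19–29 who attend only Open Gym are not in training. Table 3 also frames the sport outcome as continued engagement, although Table 1 hypothesises an increase.

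On size, dividing 10 by 26 gives 38%, but that holds only if gains stop 26 weeks after program start. With visits timed from baseline and continuing accrual, the 6-month share is 28%. Under that same accrual, the change from baseline to 6 months still spans 26 weeks of gain. The power loss therefore depends on reading the planned difference as the total change since program start.

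Finally, the bias mainly shrinks the measured gain and does not create one. Recruitment was planned through September 2019, before the registration date of October 22, 2019, so a new eligibility rule might reach few or no participants. Both points stand. They bear on severity and on the form of the fix, and do not remove the defect.

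**Conclusion.** The point holds in this form: the rules permit a baseline up to 10 weeks into programming, so a pre-program value is not secured in a study whose only comparator is baseline. The bias runs mainly toward understating gains. The sport and training outcomes can already be met at baseline if facility or partner programs count, and the article leaves that open.

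At the maximum lag, 28% of the change to the 6-month visit precedes baseline, falling to 16% at 12 months and 9% at 24 months. Power at 6 months for ages 6–12 goes from 94.9% to about 74%. With recruitment in week 1 the 6-month share is at most about 10% and power about 90%. These figures assume linear, continuing accrual, two-sided alpha of 0.05 and the same lag for everyone. The actual distribution of lags is not given, so they bound an illustration and do not estimate the loss. This should be corrected, but it does not invalidate the study.

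**What to change.** 1. Where enrolment is still possible, take baseline at registration or before the first session. Families are already approached then.
2. For those already enrolled, compute weeks and hours attended before baseline from the attendance and program-hours data described under Incentivization. Report their distribution by cohort.
3. Adjust the time effect and the dose analyses for exposure before baseline. In the repeated-measures models this means including its interaction with time, because a main effect alone does not address the change.
4. Pre-specify an analysis restricted to participants with an early baseline, for example within 3 weeks of first attendance (first-week approach plus the 2-week baseline window).
5. State whether facility and partner programs count toward regular sport and toward a training place. Where the data separate them, score both outcomes without those programs. Otherwise interpret them as retention, not as an increase.

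The cost is modest: a revised entry or baseline sentence, two outcome definitions, and use of data already collected. The main downside is a smaller sample in the restricted analysis, by an amount that cannot be known until the lags are tabulated. The existing self-report may also not allow the re-scoring in step 5.

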#### Sample size

Based on the number of variables planned for analyses in each cohort (see Table 1) [43], we will recruit *n* = 150 youth ages 6–12, *n* = 100 youth ages 13–18 years of age, and n = 150 youth ages 18–29. Statistical power calculations were conducted to justify the appropriateness of the proposed study sample sizes for each age group. For youth aged 6 to 12, statistical power for the primary outcome variable, physical literacy, was analyzed using pre-post MLSE LaunchPad member data on the PLAYself Physical Literacy Assessment tool. To achieve a large effect size (Cohen’s d > = .8; MLSE LaunchPad participant mean = 1201, SD = 258.8; study group mean = 1277), the power calculation performed suggests that the proposed sample size of 150 will yield 94.9% post-hoc power. Power calculations were conducted using data previously collected at MLSE LaunchPad for primary outcome variables of interest in the 13 to 18-year-old cohort (i.e., self-esteem, grit, resilience, physical activity status, and physical activity levels). To achieve large effect sizes for these variables, the proposed sample size of 100 will yield 99.5–100% post-hoc power. Lastly, for youth aged 19 to 29, to achieve a large effect size in the primary outcome variable, employment status, the proposed sample size of 150 will yield 100% post-hoc power (power calculated using data collected at MLSE LaunchPad).

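### Ages 6–12: the 94.9% power is attached to a large effect (d of 0.8 or more), but the printed means and SD give d = 0.29, and 94.9% is the power for that smaller effect

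*Protocol article*

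**What the plan says.** The Sample size section of the protocol article sets 150 participants for ages 6–12. It first ties the cohort sizes to the number of analysis variables, then offers power calculations to justify them. For physical literacy, the primary outcome variable at ages 6–12, it describes the effect as large and gives the threshold and inputs together: "d > = .8; MLSE LaunchPad participant mean = 1201, SD = 258.8; study group mean = 1277". It concludes that "the power calculation performed suggests that the proposed sample size of 150 will yield 94.9% post-hoc power". The inputs are said to come from pre-post PLAYself data on facility members. No test, significance level, within-person correlation or attrition is given.

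Elsewhere the article describes a single-arm, within-subject design with assessments at baseline, 6, 12 and 24 months (Study design). It plans repeated measures ANOVA for the main effect of time on physical literacy, adjusted for demographic variables (Data analysis, ages 6–12).

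**The concern.** The effect label and the numbers beside it disagree. A shift from 1201 to 1277 against an SD of 258.8 is under a third of an SD, which is far from 0.8. The power could belong to the label or to the numbers, but not to both.

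The section uses this calculation to show that 150 is an appropriate number. A reader who takes it at face value will believe that the cohort was sized for an effect of 0.8 SD or more. That reader may then judge a modest gain, or a null result, against the wrong benchmark. It is also unclear whether the figure carries over to the planned analysis. The SD is attached to a group mean, whereas power for a within-person change depends on the SD of change.

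**Working it through.** **Inputs from the Sample size section.** Reference mean and SD: "MLSE LaunchPad participant mean = 1201, SD = 258.8". Comparison mean: "study group mean = 1277". n = 150. Stated power: "94.9% post-hoc power". Significance level and sidedness are not stated; 5% two-sided is assumed.

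**Effect size.** d = (1277 − 1201)/258.8 = 76/258.8 = 0.294.

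**Reproducing the stated power.** Power = Φ(d√n − 1.96) = Φ(0.294 × √150 − 1.96) = Φ(1.637) = 0.949. This matches the printed figure. Other forms with the same inputs:

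| Form | Power |
|---|---|
| One-sample z, two-sided | 94.9% |
| One-sample t, two-sided | 94.7% |
| One-sample z, one-sided | 97.5% |
| Two groups of 75, two-sided | 43.6% |
| Two groups of 150, two-sided | 72.0% |

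**What d = 0.8 would require.** With SD 258.8, the comparison mean would be 1201 + 0.8 × 258.8 = 1408. With a 76-point difference, the SD would be 76/0.8 = 95. At d = 0.8 and n = 150, Φ(0.8 × √150 − 1.96) = Φ(7.84), which is more than 99.99%. Power of 94.9% at d = 0.8 would need only about 20 people.

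**Does 94.9% carry over to a within-person change?** Suppose 258.8 is the SD at each visit and r is the correlation between visits. Then SD of change = 258.8 × √(2(1 − r)), and power = Φ(76/SD of change × √150 − 1.96). The article does not give r, so a range is assumed:

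| Assumed r | SD of change | Paired contrast, n = 150 |
|---|---|---|
| 0.3 | 306.2 | 86.0% |
| 0.5 | 258.8 | 94.9% |
| 0.7 | 200.5 | 99.6% |

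At r = 0.5 the SD of change equals 258.8, so the paired and one-sample formulas coincide. They also coincide if 258.8 is already an SD of change.

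**The planned four-visit test of time.** Assume compound symmetry, no covariates, and mean gains of 0, 19, 38 and 76 points at 0, 6, 12 and 24 months (linear in time). Power at n = 150 is then about 76%, 90% and 99% for r = 0.3, 0.5 and 0.7. If instead the full 76 points are present from 6 months on, it is about 89%, 97% and 99.9%. These figures only illustrate how far the answer depends on inputs that are not given.

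**The case against.** The strongest reply is that the article names no test. The source is described as pre-post data, so 258.8 could be an SD of change, and 94.9% could then be a legitimate paired calculation. This stands. A reader might infer that the authors used a one-sample test against a fixed mean, which the trial will not run. The exact match makes that possible, but a paired test with SD of change 258.8 gives the same number, so the documents do not settle it. The effect-size contradiction is unaffected, because 76/258.8 is 0.29 under either reading.

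A reader might also infer that power is overstated. That is not shown: at n = 150 the paired range of 86% to 99.6% lies on both sides of 94.9%. Only the effect label is overstated.

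A third tempting step is to extend the error to ages 13–18, where the section says: "To achieve large effect sizes for these variables, the proposed sample size of 100 will yield 99.5–100% post-hoc power". Under the one-sample formula, 99.5% at n = 100 corresponds to d = (1.96 + 2.576)/10 = 0.45. However, the article prints no means, SDs or test for that cohort, and one of its variables, physical activity status, may be categorical. Other ordinary tests could give 99.5% with a large effect, so no contradiction can be shown. The same holds for ages 19–29.

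The recruitment and data-collection dates mean that not everyone can reach 24 months, which invites a much lower power figure. That figure would need assumed accrual, assumed correlations and a single baseline-to-24-month contrast in place of the planned test across visits. Incomplete late follow-up is a separate matter.

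Finally, the term post-hoc might suggest that 1277 was observed in this trial's own participants. The article does not say so.

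It is fair to add that power was supporting justification, not the sole basis for n, and that a condensed article may leave the SD of change and attrition to a fuller document. This lowers the severity. It does not excuse a label and inputs that are both printed and disagree.

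**Conclusion.** Wrong as written; it should be fixed. The label of d at least 0.8 is incompatible with the article's own inputs, which give d = 0.29: the threshold is about 2.7 times the effect used (0.8/0.294). The 94.9% belongs to d = 0.29. This rests only on the printed means, SD and n, plus a conventional two-sided 5% level.

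That 94.9% applies to the planned repeated measures analysis is not shown. If 258.8 is the SD at each visit, power for a paired contrast with all 150 contributing runs from about 86% to 99.6% over assumed correlations of 0.3 to 0.7. The direction of any error in the power is therefore unknown. No error is shown for the two older cohorts.

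**What to change.** 1. Replace the large-effect label for ages 6–12 with the effect actually used: 76 points, d about 0.29.
2. State which test and significance level produced 94.9%, and whether 258.8 is a cross-sectional SD or an SD of change.
3. Restate power for the planned within-person change, using the SD of change from the pre-post member data already held and the number expected at follow-up.
4. For ages 13–18 and 19–29, check that the large-effect label matches the inputs used, and correct it only if it does not.

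The cost is a few sentences and one recalculation from existing data. No extra participants and no change to the analysis are needed. The restated power may come out higher or lower than 94.9%.
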